# 1. Lay summary

## 1.1 Background

People who require hospital admission for COVID-19 usually have severe lung infection which means they can struggle to maintain oxygen levels. However, other organs can also be affected, with the kidneys being among the most common. Around a third of people admitted to hospital with COVID-19 develop kidney damage (known as acute kidney injury or AKI); of these, around 10% develop such severe AKI that they require short-term dialysis (treatments to clear out toxins and excess fluid from their bodies). The reasons for this AKI are yet to be definitively understood.

It is not unusual for AKI to complicate any severe illness (such as life-threatening infections or trauma), especially in people who have other medical problems such as diabetes, chronic kidney disease (CKD) or heart failure. We do not know whether AKI related to COVID-19 just reflects this or whether it is because of processes directly related to COVID-19 infection itself.

While AKI is often recoverable, it can sometimes lead to worsening long-term kidney function. Chronic kidney disease is diagnosed when kidney function declines to less than 60% of what it should be. In some cases, chronic kidney disease can lead to permanent kidney failure requiring long-term dialysis (often involving attending a dialysis unit three-times a week for four hours each time), or a kidney transplant. Even without kidney failure, chronic kidney disease is an important risk factor for several other complications including heart disease and death. The complications caused by chronic kidney disease place considerable stress on the NHS and it is important that we know what to expect to be able to ensure that services are planned with sufficient capacity to cope. For example, growing numbers requiring dialysis has a devastating impact on quality of life for those people and will require investment in the workforce and infrastructure. It can also mean more people requiring hospital admissions for heart attacks.

One way of determining what happens to kidney function after COVID-19 is to analyse readily-available health records collected from day-to-day patient care. A recent study of

this sort in US military veterans suggested that people who survived COVID-19 are more likely to develop kidney failure and lose 50% of their kidney function compared to levels before they had COVID-19. We plan to investigate this in greater detail using electronically coded NHS medical records from England using a secure, Trusted Research Environment platform called OpenSAFELY ([www.opensafely.org](http://www.opensafely.org)). OpenSAFELY comprises 40% of the general population in England (24 million people).

This study has been funded by the National Institute for Health Research (NIHR). The study was approved by the Health Research Authority and the London School of Hygiene & Tropical Medicine Ethics Board.

## 1.2 Methods

Our study will include adults not already on dialysis and not already having received a kidney transplant. We will compare people with and without COVID-19 for differences in the rates of the following kidney complications:

1. Newly-diagnosed kidney failure (i.e. new dialysis or kidney transplant, or loss of kidney function down to less than 15% of what it should be),
2. At least 50% loss in kidney function from before they developed COVID-19,
3. Further AKI (suggesting their kidneys are more susceptible to future damage).

We will be able to determine whether outcomes vary based on the severity of COVID-19 (i.e. based on whether people required hospitalisation, intensive care, a ventilator, dialysis or had AKI), based on time (e.g. during peaks, after widespread use of effective anti-COVID-19 drugs such as steroids), and based on their levels of vaccination.

In our statistical analysis, we will account for factors such as age, sex, ethnicity, socioeconomic deprivation, smoking, BMI, and pre-existing medical problems such as diabetes.

## 1.3 Strengths and limitations

As kidney failure is a relatively rare occurrence in the general population, very large studies are needed to be able to investigate whether or not a group is at increased risk compared to other groups. Because of the size of the population in OpenSAFELY, we are uniquely placed to be able to look for this in the context of COVID-19. Furthermore, we can expect the data to be comprehensive as it comes from GPs and hospitals within a national healthcare system with universal coverage.

As with other studies of this nature, we anticipate challenges associated with real-world data collection. We will be as rigorous as possible to address these limitations by undertaking multiple analyses with slight differences. For example, we will compare people with COVID-19 (including people hospitalised and not hospitalised) to different groups of people without COVID-19:

1. A historical group comprising individuals followed-up from exactly 2 years before the person with COVID-19. The reason for using a historical comparator group is because not everyone with COVID-19 gets diagnosed, especially when access to testing has been limited.
2. A contemporary group comprising individuals followed-up from the same time as the person with COVID-19. The reason for using a contemporary comparator as well is to account for changes over time during the pandemic such as differences in access to healthcare (e.g. likely to have the same access to blood tests).

A further historical analysis will be restricted only to people hospitalised with COVID-19. In this analysis, we will compare this group to people hospitalised with other lung infections from February 2018 onwards up to the start of the pandemic. This will help us understand whether any differences in kidney outcomes are specifically due to COVID-19 or due to having any lung infection severe enough to require hospital admission.

This particular study will not investigate outcomes in kidney transplant recipients. One of the reasons for this is because blood test results in OpenSAFELY come from GP records

rather than hospitals where many transplant patients have their tests done. We do intend to work around this with a different study design.

## 2. Background

During the COVID-19 pandemic, evidence has accumulated on an association between COVID-19 hospitalisation and short-term kidney outcomes such as AKI. This has led to plausible concern about longer-term kidney complications, although definitive understanding is so far limited.

### 2.1 COVID-19 and AKI

AKI describes a clinical state of potentially reversible reduction in kidney function. It is diagnosed when there is a  $\geq 50\%$  or  $\geq 26.5 \mu\text{mol/L}$  rise in serum creatinine (a biomarker of kidney function) on blood tests compared to baseline, or a reduction in urine output to  $< 0.5 \text{ ml/kg/hour}$  based on body weight. AKI is not unusual in acute illness (due to hypoperfusion and/or inflammatory processes), especially on a background of comorbidity (e.g., diabetes, CKD, heart failure), and factors including increasing age and socioeconomic deprivation also contribute.

Initial reports on the incidence of AKI in COVID-19 from China were low, and this may be because patients had fewer comorbidities and were admitted for less severe COVID-19 than in other settings. A more recent analysis of over 40,000 individuals in the International Severe Acute Respiratory and emerging Infections Consortium World Health Organization Clinical Characterization Protocol UK (ISARIC-WHO CCP-UK) study, a large prospective cohort comprising patients admitted with COVID-19 to over 250 hospitals across the UK up to early December 2020, found that 31.5% of patients developed AKI. As pre-admission serum creatinine data was unavailable, AKI could only be determined in patients who had at least 2 inpatient measurements and so it is possible people more likely to develop AKI were more likely to have repeated tests; conversely, patients with stable

elevated serum creatinine from the time off admission may have been misclassified as not having AKI resulting in underestimation. This study also found that 3% of over 80,000 inpatients required kidney replacement therapy (KRT), the treatment for severe AKI. Pre-existing CKD was strongly associated both AKI and KRT, as were physiological markers of more severe COVID-19 at hospital admission (i.e. tachypnoea and hypoxia). The variability in estimates of the incidence of AKI may reflect differences in national and local criteria for hospital admission as the risk of AKI in mild COVID-19 or asymptomatic SARS-CoV-2 infection remains unknown.

## 2.2 COVID-19 and CKD

Individuals are primarily diagnosed with CKD when they are found to have an estimated glomerular filtration rate (GFR) (eGFR) persistently  $< 60\text{ml/min/1.73m}^2$  over at least three months. eGFR is usually calculated from serum creatinine, an easily assayed endogenous marker of kidney function but one that is affected by a range of factors related to both its synthesis and excretion such as age, sex, diet, muscle mass, renal tubular secretion, gut loss, muscle catabolism and genetic ancestry. CKD can also be diagnosed by urinary albumin creatinine ratio  $>3\text{ mg/mmol}$  or in the presence of a structural kidney abnormality (e.g. polycystic kidneys or dysplastic kidneys).

Trajectories of eGFR can vary and progressive decline to  $<15\text{ ml/min/1.73m}^2$  results in end-stage renal disease (ESRD) (also known as “kidney failure”) with long-term KRT required to sustain life (in the form of dialysis or kidney transplantation). In addition to ESRD, CKD is associated with increased all-cause mortality, cardiovascular mortality and morbidity, and AKI. Complications of CKD include anaemia, hyperkalaemia, hypervolaemia, altered pharmacokinetics, and secondary hyperparathyroidism^7. CKD is common, affecting 8.5% of the UK population, and is associated with a substantial burden on healthcare costs.

AKI is a risk factor for CKD. After SARS-CoV-2 infection, tubular injury, de novo immune-mediated processes (such as collapsing glomerulopathy), or direct infection of kidney parenchyma might independently cause additional insults leading to long-term kidney

disease. In addition, pre-existing CKD is an independent risk factor for severe outcomes in COVID-19, plausibly leading to accelerated renal decline in those most at risk.

Given the scale of COVID-19 hospitalisation, including COVID-19-related-AKI, there is a pressing need to understand whether this will lead to an increased burden of CKD and its complications on health systems, given the potential stresses on resources that these will incur.

There has been a gradual increase in the number of studies focusing on post-COVID-19 complications, and some of these include the incidence or progression of kidney diseases.

## 2.3 Existing research

The strongest evidence to date comes from a cohort study of US military veterans with over 89,000 SARS-CoV-2 survivors and over 1.6 million non-infected military veteran controls. This study demonstrated increased incidence of subsequent AKI, eGFR decline  $\geq 50\%$ , ESRD, and major adverse kidney events (defined as eGFR decline  $\geq 50\%$ , ESRD, or all-cause mortality), irrespective of whether individuals were non-hospitalised, hospitalised, or admitted for critical care. Overall, ESRD rates were almost three times higher in survivors compared to individuals without known infection.

As this study compared SARS-CoV-2 survivors to contemporaneous individuals without known infection, it is possible that many of this comparator group were misclassified due to the reduced availability of testing in the early stages of the pandemic and asymptomatic infection, meaning that the strength of associations may be underestimated. Findings in military veterans may also have limited generalisability in the wider population (e.g. >90% of the overall cohort was male).

Increased long-term kidney outcomes in US military veterans not hospitalised after COVID-19 warrant further investigations. These findings are in contrast to a cohort study of 443 adults from Hamburg, Germany who had survived SARS-CoV-2 infection (over 90% of

whom had not been hospitalised), which found that eGFR was similar a median of 10 months after infection compared to that of matched population-based controls recruited before the pandemic (median eGFR 108.9 vs 109.1 ml/min/1.73m^2). The generalisability of this study may also be limited as some participants after SARS-Cov2 infection were recruited through public announcement rather than systematic sampling.

A study of patients from Wuhan, China who had survived COVID-19 hospitalisation investigated follow-up eGFR in an outpatient clinic after discharge, reporting that 35.0% of over 1300 patients had eGFR <90 ml/min/1.73m^2 (median follow-up 153 days). However, the findings are difficult to interpret because of the absence of pre-hospitalisation eGFR data (i.e. before COVID-19 illness), and the high threshold used for defining abnormal kidney function (eGFR <90 ml/min/1.73m^2). Inpatient data from the time of COVID-19 illness found that a similar proportion of those without AKI had eGFR <90 ml/min/1.73m^2, which may mean that the findings merely reflect the pre-existing prevalence of abnormal kidney function in the study population. Of survivors without AKI who had preserved eGFR during admission, 13.0% of those who attended follow-up were found to have new eGFR <90 ml/min/1.73m^2. However, eGFR below a lower threshold (e.g. <60 or <30 ml/min/1.73m^2), time taken to reach percentage decline in eGFR, and longitudinal eGFR decline using linear mixed models are likely to be more informative than eGFR <90 ml/min/1.73m^2 in evaluating kidney outcomes following infection.

The pathophysiological processes by which COVID-19 might lead to declining kidney function remain unknown. Autopsy studies of patients who have died with COVID-19 suggest that SARS-CoV-2 may directly infect the kidney, causing upregulation of profibrotic cell signalling pathways. However, since pre-existing CKD is a risk factor for death from severe COVID-19, the associations between COVID-19 and the histological features of CKD at autopsy may be distorted as there are difficulties inferring temporality: whether histological changes seen on autopsies were caused by COVID-19 or were present because people with CKD are more likely to die from COVID-19.

We will investigate the association between SARS-CoV-2 and long-term kidney outcomes using general population data on the OpenSAFELY-TPP platform, comprising

approximately 40% of the English adult population, We are well-placed to improve understanding of associations with greater precision, and are using a range of methods to address systematic biases.

### 3. Objectives

Overall, our aim is to investigate long-term kidney outcomes after recorded SARS-CoV-2 infection in the general population.

Our specific objectives are:

1. To describe the relative and absolute rates of ESRD (primary outcome) after recorded SARS-CoV-2 infection compared to both contemporary and historical groups, stratified by:
  - a. Hospitalisation for COVID-19
  - b. Critical care admission for COVID-19
  - c. Mechanical ventilation for COVID-19
  - d. Acute KRT associated with COVID-19
  - e. AKI associated with COVID-19
2. To describe the relative and absolute rates of a 50% reduction in eGFR, incident AKI, and death (secondary outcomes), after recorded SARS-CoV-2 infection compared to both contemporary and historical groups, stratified by:
  - a. Hospitalisation for COVID-19
  - b. Critical care admission for COVID-19
  - c. Mechanical ventilation for COVID-19
  - d. Acute KRT associated with COVID-19
  - e. AKI associated with COVID-19
3. To describe the relative and absolute rates of these outcomes after hospitalisation for COVID-19 compared to a historical hospitalised group, stratified by:
  - a. Critical care admission for COVID-19
  - b. Mechanical ventilation for COVID-19

- c. Acute KRT associated with COVID-19
  - d. AKI associated with COVID-19
- 4. To describe the relative and absolute rates of outcomes after recorded SARS-CoV-2 infection compared to both contemporary and historical groups stratified by:
  - a. Baseline eGFR
  - b. Diabetes
  - c. Age
  - d. Sex
  - e. Ethnicity
  - f. Socioeconomic deprivation
- 5. To describe the relative and absolute rates of outcomes after recorded SARS-CoV-2 infection compared to both contemporary and historical groups additionally stratified by:
  - a. Calendar time
  - b. Vaccination status

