### 4.4.2 Historical comparator groups

For our main analysis, historical comparator groups will comprise individuals from the general population under follow-up in OpenSAFELY, each matched five to one to each

individual from the recorded SARS-CoV-2 group on age (within 2 years), sex, NHS Sustainability and Transformation Partnership (STP, geographical areas configured for regional reorganisation available in our data), IMD decile (a measure of socioeconomic deprivation based on postcode), and date (i.e. 2 years before the first recording of SARS-CoV-2 infection in the exposed case) (Figure 1). Anyone coded in primary care or SUS to be receiving chronic dialysis or kidney transplant or with eGFR  $<15$  ml/min/1.73m^2 before this date will be excluded (i.e. anyone with ESRD or CKD Stage 5). We will match without replacement (i.e. individuals in the historical comparator group will not be matched to more than one individual with SARS-CoV-2 infection) in order to optimise statistical precision.

In a secondary analysis, we will compare individuals who remain alive 28 days after admission to hospital with COVID-19 with those who remained alive 28 days after admission to hospital for pneumonia (including influenza) from 1 February 2018 up to two years before the end of follow-up for the exposed group (unmatched) (Figure 1). A previous study done using OpenSAFELY found similarities in outcomes between people discharged after hospitalisation with COVID-19 and a historical comparator group discharged after pneumonia. Individuals who survived COVID-19 and hospitalisation from pneumonia in 2018-2019 will be followed-up in both the exposed and unexposed groups.

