#### **4.4.4 Follow-up start**

By using index dates 28 days after first recording of SARS-CoV-2 infection (i.e., date of testing in SGSS, date of primary care coding, or date of admission on SUS), we will be able to look back and further stratify the exposure by measures of SARS-CoV-2 severity (i.e. community, hospitalisation, critical care admission etc.).

For analyses comparing people after SARS-CoV-2 infection to a historical comparator group from 2018-2019, the matched historical comparators will be followed-up from exactly two years before the index date.

For analyses comparing people hospitalised for COVID-19 with an unmatched historical group of individuals hospitalised for pneumonia from 2018-2019, we will follow all eligible individuals from 28 days after their admission date for pneumonia.

For analyses comparing people after SARS-CoV-2 infection to a matched contemporary comparator group, we will follow all eligible individuals from the index date.

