## 4.5 Study measures

### 4.5.1 Exposure

We will identify recorded SARS-CoV-2 infection using data from SGSS, primary care records and SUS. We will include all codes indicative of SARS-CoV-2 infection. SGSS contains the date of an individual's earliest positive SARS-CoV-2 test results from Pillar 1

(NHS and Public Health England laboratories) and Pillar 2 (commercial partners) between 1 February 2020 to the most recent available time point (i.e. the COVID-19 pandemic era).

Individuals meet criteria for inclusion in the COVID-19 exposed group if they:

- Tested positive for SARS-CoV-2 infection in SGSS
- Had a primary care code indicative of SARS-CoV-2 infection
- Discharged from hospital with an International classification of Diseases Version 10 (ICD-10) code in SUS indicative of COVID-19

The index date for those exposed to COVID-19 will be from 28 days after first recording of SARS-CoV-2 infection (i.e., after the earliest date of the record of a positive test in SGSS, primary care coding, or admission in SUS).

Looking at all identified SARS-CoV-2 infections will allow us to investigate how many adverse kidney outcomes can be prevented by preventing SARS-CoV-2 infection altogether through comparisons with people from the general population without known infection. We will also be able to investigate whether outcomes vary based on infection severity (hospitalisation, critical illness, mechanical ventilation and AKI [including requiring RRT]) as well as calendar time and vaccination status through further stratification based on morbidity coding (ICD-10 codes) from SUS. We will categorise people as i) unvaccinated if they had not received any vaccine dose at least 7 days before first recording of SARS-CoV-2 infection, ii) single dose vaccinated if they had received one vaccine dose at least 7 days before first recording of SARS-CoV-2 infection, iii) double vaccinated if they had received two vaccine doses at least 7 days before first recording of SARS-CoV-2 infection, and iv) more than double vaccinated if they had received more than two vaccine doses (including booster doses) at least 7 days before first recording of SARS-CoV-2 infection.

Hospitalised COVID-19 cases will be further investigated through a separate comparison with a historical group. Additional levels of exposure for those hospitalised will include critical care admission, mechanical ventilation, acute KRT and AKI, determined from ICD-10 and procedural codes in SUS.

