### **4.6.3 Secondary analyses**

1. We will use Cox regression models to estimate cause-specific hazard ratios and 95% confidence intervals for the secondary outcomes i) 50% reduction in eGFR, ii) AKI and iii) death for individuals after SARS-CoV-2 (stratified as above) compared to individuals in the i) historical and ii) contemporary comparator groups.
2. We will undertake further Cox regression models for both primary and secondary outcomes with SARS-CoV-2 infection stratified by calendar time (i.e. February –

June 2020, July – September 2020, October – November 2020, December 2020 – February 2021, and March – January 2022) and vaccination status.

3. We will fit interaction terms to obtain cause-specific hazard ratio estimates for both primary and secondary outcomes stratified by age group, ethnicity, socioeconomic deprivation, diabetes and baseline eGFR.
4. For people who survive 28 days after hospitalisation for COVID-19, we will undertake an unmatched cohort analysis comparing kidney outcomes with a historical population followed-up from 1 February 2018 restricted to those who survived 28 days after a hospital admission for pneumonia (with or without influenza). This analysis will be stratified by critical care admission, mechanical ventilation, acute KRT and AKI, with additional adjustment for calendar month. The reason for this analysis is to investigate whether COVID-19 is responsible for long-term kidney outcomes to a greater or lesser extent than hospitalisation for other respiratory tract infections.

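### In the hospitalised COVID-19 versus pneumonia comparison, severity strata are defined for COVID-19 only; read that way, the stratum hazard ratios mix severity with any COVID-19 effect

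*Protocol*

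**What the plan says.** Objective 3 (Protocol, section 3) reads "To describe the relative and absolute rates of these outcomes after hospitalisation for COVID-19 compared to a historical hospitalised group, stratified by", followed by four items. The first is "Critical care admission for COVID-19"; ventilation, acute KRT and AKI are also tied to COVID-19 by their wording.

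Section 4.5.1 introduces the comparison with "Hospitalised COVID-19 cases will be further investigated through a separate comparison with a historical group" and continues: "Additional levels of exposure for those hospitalised will include critical care admission, mechanical ventilation, acute KRT and AKI". Section 4.4.4 gives the 28-day delay before follow-up as the means of grading the exposure by severity of SARS-CoV-2 infection.

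The pneumonia arm has no such levels. Section 4.4.2 defines it as people alive 28 days after a pneumonia admission, unmatched, and section 4.4.4 says "we will follow all eligible individuals from 28 days after their admission date for pneumonia".

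The analysis itself is specified in section 4.6.3 item 4: "This analysis will be stratified by critical care admission, mechanical ventilation, acute KRT and AKI, with additional adjustment for calendar month". That sentence does not say whether the strata apply to one arm or both. The next sentence gives the purpose, with admissions for respiratory infections other than COVID-19 as the yardstick: "The reason for this analysis is to investigate whether COVID-19 is responsible for long-term kidney outcomes to a greater or lesser extent than hospitalisation".

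**The concern.** Against the general population, grading only the exposed group is workable, because those comparators have no index admission to grade. Against another hospitalised group it is not. Pneumonia patients can also need critical care or ventilation and can also develop AKI. The protocol itself notes that AKI is common in acute illness (section 2.1) and is a risk factor for CKD (section 2.2).

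If only COVID-19 is graded, each severe stratum is compared with a mixture of mild and severe pneumonia. The resulting hazard ratio contains the effect of severity as well as any effect of COVID-19. A reader could take a raised hazard ratio for COVID-19 with AKI as evidence of a COVID-specific process when AKI after any respiratory admission would give the same result. That is the distinction this analysis is meant to draw.

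Nothing else in the plan removes the problem. The adjustment sets in section 4.6.2 contain no severity measure from the index admission, item 4 adds only calendar month, and no sensitivity analysis in section 4.6.4 addresses it. Section 6 urges caution because the two survivor groups may differ in susceptibility and survival, but does not mention a severity mismatch.

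**Working it through.** **The plan's own figures.** The protocol gives no number for this comparison. Its only computed figures are the power estimates in Table 1, which rest on general-population ESRD incidence. The 88% for 200,000 exposed and a hazard ratio of 1.6 reproduces as 87.5% (two proportions, 0.02% incidence, 5:1, two-sided 5%), but it has no bearing here.

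**Inputs, both assumed.**
- a: share of pneumonia 28-day survivors who had AKI during the index illness. Taken as 0.1 to 0.3. Section 2.1 gives an AKI figure (31.5%) for COVID-19 inpatients, not for pneumonia.
- R: ESRD hazard with AKI divided by that without, the same in both arms. Taken as 3 to 10. It should be read as net of whatever covariates are adjusted for.

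**Set-up.** Let COVID-19 have no effect (true hazard ratio 1). With hazard h in people without AKI and hR in people with AKI, the ungraded pneumonia arm has average hazard h(1 - a + aR). Treating the hazard ratio as a ratio of rates, which is reasonable for a rare outcome:
- COVID-19 with AKI versus all pneumonia: R / (1 - a + aR)
- COVID-19 without AKI versus all pneumonia: 1 / (1 - a + aR)

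| a | R | 1 - a + aR | AKI stratum | No-AKI stratum |
|---|---|---|---|---|
| 0.1 | 3 | 1.2 | 2.50 | 0.83 |
| 0.1 | 10 | 1.9 | 5.26 | 0.53 |
| 0.3 | 3 | 1.6 | 1.88 | 0.625 |
| 0.3 | 10 | 3.7 | 2.70 | 0.27 |

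The same formula serves for any severity marker. Over a wider grid (severe share 5% to 30%, rate ratio 2 to 10), the severe-stratum value runs from 1.54 (30%, 2) to 6.90 (5%, 10).

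**Same definition in both arms.** The comparison becomes hR against hR, or h against h, so the hazard ratio is 1.00 in each stratum.

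**Overall contrast.** With severe shares c in COVID-19 and p in pneumonia, the ratio is (1 - c + cR) / (1 - p + pR). If c = p = 0.10 it is 1.00. If c = 0.15 and p = 0.05, it is 1.15/1.05 = 1.10 at R = 2 and 2.35/1.45 = 1.62 at R = 10. The overall hazard ratio therefore moves only if the case mix differs between arms, which is a separate matter from how the strata are defined.

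**The case against.** The strongest reply is that section 4.6.3 item 4 is the operative specification. There the strata belong to the analysis, not to COVID-19, and a stratified two-group analysis can naturally mean strata in both groups. Which code lists apply to the comparator's admission could also be left to an analysis plan that is not shown. This stands in part: a reader might infer that the protocol declares pneumonia a single undivided reference, and it does not. But wherever the strata are defined they are tied to COVID-19, so the sections need reconciling; this is more than missing detail.

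Second, a reader might infer that the whole comparison measures severity and not COVID-19. The protocol does not support that. The overall contrast of hospitalised COVID-19 with hospitalised pneumonia is unaffected by undefined pneumonia strata and goes first to the stated purpose. Even the stratum results, set against a common reference, have descriptive value as a severity gradient.

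Third, a and R are not in the protocol, so the size is illustrative. This stands. Only the direction is firm, for any R above 1.

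Fourth, AKI and critical care arise after infection, and section 2.2 presents AKI as a route to CKD. A contrast within AKI conditions on a possible mediator, so it is a different estimand and not a pure correction. This stands and belongs in the interpretation.

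Fifth, the deviations table reports that ventilation and acute KRT were dropped as exposure levels, and that interactions by critical care or AKI were thought hard to interpret because of competing death. That reduces what remains to settle but defines no level for pneumonia.

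**Conclusion.** The concern holds for the severity-stratum hazard ratios of one secondary analysis. Objective 3 and section 4.5.1 define the strata for COVID-19 only, section 4.6.3 item 4 is ambiguous, and the pneumonia admissions are nowhere graded. Read that way, the stratum hazard ratios depart from 1 even when COVID-19 has no effect: about 1.9 to 5.3 with AKI and 0.27 to 0.83 without, under the assumed a of 0.1 to 0.3 and R of 3 to 10.

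The overall COVID-19 versus pneumonia hazard ratio and the primary ESRD analyses against the matched general-population groups are not touched. The issue is moderate: it should be clarified before the stratum results are interpreted, but it does not undermine the study.

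**What to change.** Reconcile objective 3, section 4.5.1 and section 4.6.3 item 4:

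1. State that the severity levels that are retained apply to the index admission in both arms, using the same SUS code definitions over the 28 days after admission.
2. Report the COVID-19 versus pneumonia contrast within each level, from a group-by-severity interaction.
3. Keep the unstratified contrast as the main estimate of this analysis.
4. If severe COVID-19 is still shown against all pneumonia, label it a severity gradient that does not isolate COVID-19.

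The cost is running the existing code lists on the pneumonia admissions and adding an interaction term. There are two downsides. Intervals will be wider where pneumonia strata are small. The within-level contrasts also condition on events after admission that may carry part of the COVID-19 effect, so the report should say so and not present them as total effects.
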